### Clinical activities

The Clinical Activities Questionnaire, developed by the research team, includes 33 clinical activities that may be performed by advanced practice nurses. Examples include prescribing analgesics, adjusting medication dosages and making decisions regarding patient admission or discharge. Participants indicate, on a 5-point Likert scale (1=disagree to 5=agree), the extent to which they consider these activities appropriate for advanced practice nurses. Because of Austria’s restrictive legal framework,^34^ insights from clinical practice are especially valuable for advocating an expanded scope of practice for advanced practice nurses. The questionnaire was developed following the same procedures as the Core Questionnaire, including expert review, cognitive pretesting using the think-aloud method and empirical testing with a target population sample.^14^

### Data collection

Healthcare professionals from relevant departments and units will be invited to participate in the online survey. Recruitment will occur through posters and flyers. Participants will receive an email containing the survey link and informed consent. Data collection will occur over a minimum of 8 weeks, with regular reminders sent throughout the period.

### Data analysis

Data analysis will be conducted using IBM SPSS Statistics V.29.0.2.0. Statistical analyses of validated instruments will follow the recommendations of the original authors. The core and supplementary questionnaires developed for this study will first be analysed at the item level to determine frequencies and percentages. Mean scores will then be calculated for the clinical, professional and organisational dimensions. Subgroup comparisons between dependent and independent variables will test for statistically significant differences based on scale levels and distribution characteristics. Depending on the level of measurement and data normality, χ^2^ tests, Mann-Whitney U tests, Kruskal-Wallis tests (with Bonferroni-Holm correction), or independent samples t-tests will be used. Normality of metric variables will be assessed using the Shapiro-Wilk test, which demonstrates high sensitivity, particularly in smaller samples.^35^ Statistical significance will be set at alpha (α) ≤0.05.

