#### Participants and recruitment

At the University Hospital Salzburg, a total of 22 advanced practice nurses are currently employed. Based on the organisational structure and staffing levels of the participating departments, the eligible population for the remaining cohorts comprises 498 registered nurses and nurse assistants, 49 nurse managers and 183 physicians. Participant recruitment will follow a top-down approach, beginning with the advanced practice nurses. If an advanced practice nurse in a department meets the inclusion criteria, all registered nurses, nurse assistants, nurse managers and physicians working in the respective advanced practice nurse’s clinical unit will also be eligible, provided they meet the inclusion criteria shown in figure 3. The study will employ a census, non-probabilistic design that includes all participants who meet the predefined selection criteria.^14^

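### A Shapiro-Wilk pretest picks t-test or Mann-Whitney for two-group score comparisons, so with cohorts of 22 to 498 sample size largely decides whether means or ranks are compared

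*Protocol article*

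**What the plan says.** Under Data analysis (quantitative phase), the article first describes how the self-developed questionnaires are scored: "Mean scores will then be calculated for the clinical, professional and organisational dimensions". It then gives the rule for choosing a test. "Depending on the level of measurement and data normality", the analyst takes a χ² test or one of the following: "Mann-Whitney U tests, Kruskal-Wallis tests (with Bonferroni-Holm correction), or independent samples t-tests will be used". Normality is judged by one named procedure with one stated reason: "Normality of metric variables will be assessed using the Shapiro-Wilk test, which demonstrates high sensitivity, particularly in smaller samples". The threshold is "Statistical significance will be set at alpha (α) ≤0.05". No graphical criterion, skewness limit or fixed test per outcome is given, and no Welch version of the t-test is named.

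Under Participants and recruitment, "a total of 22 advanced practice nurses are currently employed", and the other eligible groups are "498 registered nurses and nurse assistants, 49 nurse managers and 183 physicians". These are ceilings before non-response, because the design is a census.

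**The concern.** A normality test answers whether a departure from normality can be detected. The analyst needs to know whether the departure matters for the comparison. Detection depends heavily on n, whereas a test on means becomes less sensitive to skew as n grows. With cohorts that differ more than twentyfold in size (498/22 = 22.6), a pretest tends to pass skewed scores in the smallest group, where skew could matter, and to reject them in the large groups, where it matters least.

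Two things are at stake. First, the article reports mean scores, but a Mann-Whitney p-value does not test a difference in means. Results for one score would then not be comparable across cohort pairs. Second, the pretest looks at shape and not at spread, and with group sizes this unequal a difference in spread is what moves the error rate.

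**Working it through.** **Inputs from the article.** Maximum cohort sizes are 22, 49, 183 and 498. The core questionnaire has 48 five-point items over three dimensions. Alpha is 0.05.

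**Assumptions, not in the article.** 16 items per dimension (48/3); full response; two-sided testing; the t-test is the equal-variance form; the t-test is used only if both groups pass Shapiro-Wilk; an SD ratio of 1.5 where spreads differ. The article does not list its two-group comparisons, so cohort pairs serve as the example. It states no power or error figure, so there is nothing to reproduce.

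**Step 1: how often Shapiro-Wilk rejects at 0.05** (2,000 simulated samples per cell).

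| Score distribution | n=22 | n=49 | n=183 | n=498 |
|---|---|---|---|---|
| Normal | 5% | 6% | 5% | 5% |
| 16-item mean, skew −0.07 | 4% | 5% | 9% | 35% |
| 16-item mean, skew −0.39 | 9% | 19% | 84% | 100% |
| 16-item mean, skew −0.70 | 27% | 68% | 100% | 100% |

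A separate simulation at skew about −0.5 gave 11% at n=22, 91% at 183 and 100% at 498. If only half of the largest cohort responded (n=249, an assumption), rejection at skew −0.39 would still be 97%.

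**Step 2: which test results, for one and the same distribution.** The chance of reaching the t-test is (1 − rejection in group 1) × (1 − rejection in group 2). At skew −0.39:

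- 22 v 49: 0.914 × 0.811 = 0.74 (simulated 75%)
- 22 v 183: 0.914 × 0.165 = 0.15 (simulated 13%)
- 22 v 498: 0.914 × 0 = 0 (simulated 0%)

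At skew about −0.5 the simulated shares were 63%, 7% and 0%. Only the group sizes changed between these pairs.

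**Step 3: type I error when both groups share one distribution.** At skew −0.39 the two-stage rule gave 5.4% (22 v 49), 4.9% (22 v 183) and 4.3% (22 v 498). The switch alone does no visible damage here.

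**Step 4: type I error with equal means and unequal spread.** For the equal-variance t-test, let R = (s₁²/n₁ + s₂²/n₂) / [s_p²(1/n₁ + 1/n₂)]. The error is then about 2[1 − Φ(t_crit/√R)]. For 22 v 183 with SDs 1.5 and 1:

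- true variance: 2.25/22 + 1/183 = 0.1077
- s_p² = (21 × 2.25 + 182 × 1)/203 = 1.129, so the variance the test assumes is 1.129 × (1/22 + 1/183) = 0.0575
- R = 0.1077/0.0575 = 1.87 and √R = 1.37; 1.972/1.37 = 1.44, which gives about 15%

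The simulated value for this t-test was 16.2%. Simulation of the alternatives on normal scores, smaller group more variable:

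| Pair | Two-stage rule | Mann-Whitney alone | Welch |
|---|---|---|---|
| 22 v 49 | 8.5% | 6.6% | 4.4% |
| 22 v 183 | 16.3% | 10.3% | 5.7% |
| 22 v 498 | 16.5% | 9.4% | 4.9% |

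On skewed Likert scores with the same SD ratio, the two-stage rule gave 9–11% when the smaller group was more variable and 2–3% when it was less variable. Welch gave 5–6%.

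**Step 5: the sensitivity claim.** At n=22 and skew 1.0, Shapiro-Wilk detected 32%, against 19% for Lilliefors and 20% for Jarque-Bera. It is the best of the three and still misses about two thirds.

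**The case against.** The strongest reply is that the practical harm is small, and much of that reply stands.

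- **Error rate.** A reader might infer that pretesting as such inflates type I error. Step 3 does not support that.
- **The 16% figure.** A reader might take it as the general consequence of the rule. It belongs to normal scores with an assumed SD ratio. With skewed scores at 22 v 498 the rule practically never reaches the t-test. What remains is the 9–11% or 2–3%, which at that pair comes from the rank test responding to unequal spread. The article gives no SDs, and naming the t-test without a variance option does not commit it to the equal-variance form.
- **Scope.** A reader might infer that sample size decides every analysis. For more than two groups only Kruskal-Wallis is listed, so there is no parametric alternative to switch to. Measurement level and true shape also count: near-symmetric scores mostly pass even at n=183.
- **The rationale.** A reader might call the sensitivity claim plainly false. Read as a comparison with other normality tests it is defensible (Step 5). It fails only as an absolute statement.
- **Consequences.** The study is a census with largely descriptive output, and the first integration point selects topics by mean scores and descriptive differences, not by p-values.

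The reply does not remove the rule itself. The article states it and gives a reason, so it is not a detail left to a fuller plan.

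**Conclusion.** The point holds for two-group comparisons of metric scores. For one moderately skewed score, the rule ends in a t-test in about 63–75% of runs at 22 v 49, 7–13% at 22 v 183 and 0% at 22 v 498. Whether means or ranks are compared is thus largely a matter of sample size.

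The effect on error rates is conditional. It is negligible if the groups share one distribution. Under an assumed 1.5-fold SD difference it is about 9–11% or 2–3% on skewed scores, and up to about 16% on normal scores, against about 5% for Welch. These figures rest on the assumed item count, skew, full response, SD ratio and equal-variance t-test. Non-response among the advanced practice nurses would lower the pretest's sensitivity further: at n=10 it rejects in about 5–15% of samples over the shapes tried. The documents do not support a claim that the quantitative results as a whole are invalid.

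**What to change.** In the Data analysis section:

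- Remove Shapiro-Wilk as the selector of the test. Delete the sensitivity claim, or reword it as a comparison with other normality tests.
- Name the Welch t-test in advance, with a 95% confidence interval for the difference in means, for two-group comparisons of dimension means and scale scores.
- Name rank or ordinal methods in advance for single Likert items.
- Inspect distributions graphically and report what is seen, without changing the test.

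The cost is about two sentences of wording and no extra data. Welch may have slightly less power than a rank test when scores are strongly skewed. In return, each reported mean difference has a matching interval and p-value in every cohort pair.

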### Data integration on the first integration point (INTEG 1)

After completing the quantitative phase, the first integration point will involve identifying quantitative findings that require further clarification. Particular attention will be given to surprising, inconsistent or unexpected results, which will inform the design of the qualitative phase.^15^ In line with the explanatory sequential design, decisions regarding sample composition and the thematic focus of the interviews (dimensions) will be based on the quantitative results.^18^ Following the ‘Connecting’ integration technique, the quantitative data will be linked to the qualitative phase through purposive sampling.^36^ A participant selection display^16
17^ will be developed to identify quantitative findings that warrant deeper exploration and to guide the selection of participants for the qualitative phase.^15^ Quantitative findings will first be examined within each study population and subsequently across study populations to identify findings requiring qualitative follow-up and to determine which study populations should be included in the qualitative phase. Particular attention will be given to unexpected or contradictory findings, notably high or low mean scores, heterogeneous responses, descriptively noticeable differences between study populations and findings that deviate from existing literature. These findings will be integrated into a participant selection display in tabular form, documenting the quantitative results selected for follow-up, the rationale for their selection and the study populations from which participants will be recruited. The display will subsequently inform purposive sample selection and the thematic focus of the interview guides.

## Qualitative phase

To expand, explain and deepen the quantitative findings,^15^ the qualitative phase of this explanatory mixed methods design will explore healthcare professionals’ experiences concerning the clinical, professional and organisational effects of advanced practice nurses’ role development and implementation.

### Sampling/recruitment

All participant cohorts (advanced practice nurses, registered nurses, nurse assistants, nurse managers and physicians) included in the quantitative phase are considered potential sources for the qualitative phase. Consistent with the study’s objectives, the inclusion of advanced practice nurses in the qualitative phase is ensured. Based on the participant selection display,^16^ a purposive sampling approach will be employed, including only individuals who participated in the online survey and meet the inclusion criteria presented in figure 3.

### Data collection

Qualitative data collection is planned through semi-structured, face-to-face expert interviews^37^ with advanced practice nurses and focus group discussions^14
38^ with the other cohorts selected according to the quantitative findings. The specific formats may be refined based on the emerging quantitative results. Expert interviews aim to elicit advanced practice nurses’ experiential and practical knowledge, as well as their implicit understanding of institutional processes.^37^ Focus group discussions represent a structured form of group interview led by a moderator using a semi-structured interview guide and focused on a defined topic.^14^ These discussions aim to reveal participants’ personal and non-public opinions and attitudes^38^ and are particularly suitable for mixed-methods studies.^14^ Focus groups will ideally include between four and eight participants.

### Data analysis

From the current perspective, qualitative data analysis will be conducted using reflexive thematic analysis^39^ in MAXQDA (VERBI-Software). However, the approach may be refined depending on the quantitative results. Reflexive thematic analysis provides flexibility by allowing both inductive and deductive theme development, as well as latent and semantic coding, acknowledging that these approaches represent points along a continuum rather than opposing categories.^39^ A more deductive orientation to reflexive thematic analysis emphasises a researcher-informed or theory-informed perspective, in which the developed codes reflect conceptual ideas to be explored and interpreted within the data set. In such cases, frameworks or theories serve as an ‘*…*interpretative lens through which to code and make meaning of the data’ (38, p. 57). This approach was selected to enable a deeper exploration of the dimensions and subdimensions identified through the quantitative findings and to support a theory-informed interpretation of the qualitative data. Reflexive thematic analysis with a predominantly deductive orientation was chosen for its adaptability and capacity to capture complex and nuanced experiences related to implementing advanced practice nurses’ roles. Given the explanatory purpose of the qualitative phase and its integration with quantitative results, this method facilitates the identification of both semantic and latent themes, recognises the researcher’s active interpretive role^39^ and promotes understanding of the clinical, professional and organisational effects of advanced practice nurses’ role development and implementation.

### Data integration on the second integration point (INTEG 2)

Data integration at the second integration point (INTEG 2) aims to deepen and enhance quantitative findings through qualitative results. A joint display will be developed, incorporating the clinical, professional and organisational dimensions, to demonstrate the connection between quantitative and qualitative findings and to illustrate how qualitative insights enrich the understanding of quantitative results.^15^ The integration technique ‘explaining’ will be applied to gain deeper insights into quantitative data through qualitative findings, including mixed-methods meta-inferences.^16
17^

### Mixed methods validity

We will apply the mixed-methods quality criteria proposed by Creswell and Plano Clark^15^ to guide the methodological design and execution of this study. As both quantitative and qualitative processes are employed, phase-specific quality criteria will be observed. The quantitative phase will be guided by established quality criteria for quantitative research, including construct validity, internal validity, external validity and statistical inference validity, as described by Döring.^14^ Accordingly, validated instruments with established psychometric properties were included in this study. Limitations related to the use of self-developed instruments are addressed in the ‘Strengths and limitations’ section. The qualitative phase will be guided by the trustworthiness criteria of credibility, transferability, dependability and confirmability.^14^

## Ethics and dissemination

The study was reviewed by the Ethics Committee of the Federal State of Salzburg. The Ethics Committee classified the study as not requiring formal ethical approval or further review (415-EALL/4/233/3-2025). This decision was based on the fact that the study exclusively involves healthcare professionals, does not include patient participation or patient-related data and does not constitute a clinical trial. The study adheres to the ethical principles of the Declaration of Helsinki,^40^ and complies with the European Union General Data Protection Regulation.^41^ For both the qualitative and quantitative phases, informed consent will be obtained from all participants. They will receive detailed information regarding the study’s objectives, potential implications, voluntary participation and data confidentiality. Quantitative data will be anonymised, and qualitative data will undergo pseudonymisation before analysis. Study findings will be disseminated through publications in peer-reviewed scientific journals and presentations at national and international conferences. In addition, results will be shared with study participants through internal dissemination events organised within the institution.

## Discussion

This study protocol outlines an explanatory sequential mixed-methods study,^15^ designed to evaluate the clinical, professional and organisational impact of implementing and developing the roles of advanced practice nurses in selected departments of an Austrian university hospital. The study incorporates perspectives from advanced practice nurses and other healthcare professionals at the system level. During the quantitative phase, both validated and self-constructed survey instruments will be employed. The qualitative phase builds on the quantitative findings to provide deeper insight into the results.^15^ Qualitative data will be collected through semi-structured expert interviews and focus group discussions and analysed using reflexive thematic analysis.^39^ The integrated findings will be presented in a joint display.^15^

Given the ongoing development of advanced practice nurse roles in Austria, including the absence of clearly defined advanced competencies, scope of practice and regulatory structures,^7^ focusing solely on effectiveness outcomes may obscure the broader impact of advanced practice nurses and underestimate their potential contributions.^6^ Therefore, consistent with international recommendations,^6^ this study examines healthcare professionals’ experiences and the indirect effects of advanced practice nurses’ roles, including their influence on interprofessional collaboration, communication, contribution to organisational goals and the acceptance of advanced practice nurse roles.

From a methodological perspective, the development, implementation and evaluation of advanced practice nurse roles align with the characteristics of complex interventions. Complex interventions encompass multiple components, settings, stakeholder groups and levels of influence, with strong interdependencies between the intervention and its context.^42^ Skivington *et al*^42^ recommend moving beyond an exclusive focus on outcomes toward a more comprehensive approach that evaluates overall impact. Such an approach considers how the intervention functions, interacts with its context and contributes to system-level change, including shifts in relationships, policies or social norms.^42^ To address the organisational context, this study employs the Organisational Readiness for Implementing Change instrument to assess healthcare professionals’ readiness to implement advanced practice nurse roles in selected departments of the University Hospital Salzburg.^25^ Furthermore, structural empowerment will be assessed using the Conditions of Work Effectiveness Questionnaire II^28^ to determine how supportive advanced practice nurses perceive their organisational environment in relation to role implementation. To the best of our knowledge, this is the first study to apply both instruments specifically to evaluate advanced practice nurse roles and their impact within healthcare settings.

As the implementation of advanced practice nurses at the University Hospital Salzburg is ongoing, with new advanced practice nurses continually developing and establishing their roles, the results of this study may identify opportunities for optimisation and inform future implementation efforts. Insights regarding facilitators, barriers and areas for improvement may strengthen the evidence base and serve as a resource for other healthcare institutions seeking to introduce or enhance advanced practice nursing roles. This mixed-methods study provides an opportunity to deepen understanding of the impact of advanced practice nurses’ role development and implementation across multiple dimensions and from the perspectives of diverse healthcare professionals adopting a hospital-wide, system-level approach. This perspective is essential because the effectiveness, acceptance and sustainability of advanced practice nurse roles are influenced by contextual and organisational factors.^2^ Integrating quantitative and qualitative findings will enable a comprehensive, system-level understanding of role implementation within the hospital context. A purely quantitative design without a qualitative component is often insufficient for investigating complex interventions, as qualitative or mixed-methods approaches are necessary to explore questions extending beyond effectiveness.^42^ Accordingly, integrating quantitative and qualitative data will yield deeper insights into mechanisms of change, contextual dynamics and system-level effects.

